## Abstract

Tumor-associated macrophages (TAMs) are key drivers of brain tumor progression and therapy resistance. Clinically applicable biomarkers capable of evaluating TAM populations *in vivo* are highly sought, with one potential imaging marker being ultrasmall superparamagnetic iron oxide nanoparticle (USPIO)-enhanced MRI. Ferumoxytol is a commercially available, now FDA-approved USPIO contrast agent, which circulates for up to 24 hours before undergoing extravasation and TAM-mediated phagocytosis. This study investigates the feasibility of USPIO-enhanced MRI as a noninvasive marker of TAM-associated inflammation in suspected transforming gliomas and vestibular schwannoma (VS). Patients undergo MRI at four timepoints over three days. Following an initial gadolinium-based MRI protocol, participants receive a slow ferumoxytol infusion (5 mg/kg, max 510 mg), with imaging performed immediately post-infusion and at 24 and 48 hours. Tumor tissue obtained at surgery is then analyzed to determine the cellular localization of USPIO internalization. This pilot study aims to characterize USPIO uptake and clearance within the tumor microenvironment, define the distribution and phenotype of USPIO-internalizing TAMs, and identify optimal imaging methods for this TAM quantification. By enabling *in vivo* characterization of TAM-rich regions, this work may support USPIO-enhanced MRI as a clinical biomarker of inflammation that can inform patient selection for immunomodulatory therapies.

Trial Registration Number: NCT06572475

## Introduction

1.

### Background and rationale

1.1.

The official title of this study is: USPIO Enhanced MR Imaging in CNS Tumors (UMIC): A pilot study of ferumoxytol (Feraheme®) as an imaging biomarker of tumor-associated macrophage infiltration in vestibular schwannomas (VS) and low-grade gliomas (LGG) (Clinicaltrials.gov identifier: NCT06572475 [1]). The purpose of this single-center, prospective, observational imaging pilot study is to evaluate whether a commercially available iron oxide nanoparticle, ferumoxytol, can serve as a quantitative imaging biomarker of tumor-associated macrophage (TAM) burden in central nervous system tumors, with an initial exploratory focus on suspected transforming LGGs and VS.

#### The role of TAMs in the growth and progression of CNS tumors

1.1.1.

Low-grade gliomas (LGGs), including diffuse astrocytomas, account for approximately 10–20% of all primary brain tumors. Although they are more indolent relative to grade III (anaplastic) or grade IV tumors including glioblastomas (GBMs), over 95% of LGGs will undergo malignant transformation into a higher grade (III/IV) gliomas (HGGs) [2]. Depending on tumor location, glioma typically present with seizures, focal neurological signs, or symptoms of raised intracranial pressure and these tumors have a disproportionate impact on patients and wider society, often affecting young adults [3]. In other non-CNS cancers, TAMs are known to be pivotal in driving malignant transformation and may contribute to an LGG’s propensity for infiltration, recurrence and therapy resistance [4–7]. Currently, the appearance of focal contrast enhancement within these tumors, suggestive of loco-regional blood–brain barrier (BBB) disruption, is the most used sign of tumor progression in clinical practice. However, this lacks specificity, with the temporal relationship between histological transformation and appearance of new contrast enhancement unclear [8,9].

VS are histologically benign tumors, arising from Schwann cells lining the vestibulocochlear nerve at the cerebellopontine angle [10]. Whilst 95% occur as a unilateral, sporadic tumor, they can also occur bilaterally as part of the syndrome NF2-related Schwannomatosis (NF2-SWN) [11]. The associated morbidity of VS and their treatment (surgery or radiosurgery) makes management through surgery or radiotherapy particularly challenging [12]. *Ex vivo* VS tissue analysis studies have shown that TAMs compartmentalize within Antoni type B areas and are associated with increased tumor size and growth rate [13]. *In vivo* evidence for increased TAM-dependent inflammation with growing VS also stems from TSPO positron emission tomography (PET) studies, where inflammation in growing tumors is attributed to the abundance of TAMs [13]. Subsequent work demonstrated that TAMs are a targetable driver of the immune microenvironment and tumor growth in NF2-SWN-associated VS also [14–16].

#### Imaging CNS TAMs using USPIO-enhanced MRI

1.1.2.

Considering the role of TAMs in tumor growth, paired with the advent of TAM–targeted cancer immunotherapies, a diagnostic tool capable of detecting, quantifying and monitoring TAM abundance *in vivo* is required. One potential tool, is through ultrasmall superparamagnetic iron oxide (USPIO) nanoparticles (<50 nm), consisting of an iron oxide core surrounded by a carbohydrate or polymer coating [17]. Ferumoxytol is a commercially available USPIO preparation that has FDA approval as an iron replacement therapy and most recently as an MRI contrast agent (Feraheme®, Azurity Pharmaceuticals) [18,19]. The iron USPIO core of ferumoxytol induces strong T_1_ and T_2_/T_2_* relaxation effects, and its size and coat results in a long circulating half-life following intravenous administration (ferumoxytol, t½ = 14–21 hours) [17,20]. Early phase USPIO imaging (<24 hours post-injection) allows for high-resolution MRI angiography whilst circulating in the vasculature. In areas of endothelial disruption, such as within CNS tumors, USPIO slowly (~24–48 hours) extravasates into the tissue extravascular-extracellular space (EES), showing delayed signal enhancement on T_1_-weighted imaging [21]. Ferumoxytol is rapidly phagocytosed by TAMs, as outlined in Figure 1 [22–24]. The engulfment and focal concentration of USPIO within TAMs creates local magnetic susceptibility effects, reducing signal intensity on T_2_* and susceptibility-weighted MRI acquisitions.

**Figure 1. f0001:**
[figure not shown]
Distribution and biometabolism of USPIO following intravenous administration. Following intravenous injection, USPIO nanoparticles initially circulate within the bloodstream (<24 hours; intravascular phase), producing T_1_and T_2_* shortening. In regions of blood–brain barrier disruption, USPIO extravasate over 24–48 hours into the extravascular space and are phagocytosed by TAMs, leading to intracellular iron accumulation and delayed T_1_and T_2_/T_2_* contrast changes. At later time points (>14 days), USPIO are taken up by the mononuclear phagocyte system, with iron incorporated into systemic iron stores and nanoparticle coatings cleared from the body.

Early studies utilizing USPIO in WHO grade IV gliomas demonstrated additional areas of enhancement on delayed imaging, when compared to standard post-GBCA (gadolinium-based contrast agent) sequences [22]. More recently, post-treatment studies in HGGs undergoing chemoradiotherapy have demonstrated that delayed USPIO-enhanced MRI can differentiate pseudoprogression (transiently increased volumes of contrast enhancement within the radiation field) from true disease progression in IDH-1 (isocitrate dehydrogenase 1) wild-type and IDH-1 mutated tumors [25]. Whilst a growing number of studies have investigated USPIO-related enhancement and uptake in HGGs, no studies have investigated the utility of these clinically available USPIO compounds in diffuse or transforming LGGs [7,25–28]. Therefore, it is unclear how the lesser degree of BBB disruption, and the immune phenotype in these tumors (compared to HGGs), will impact both extravasation of USPIO and its cellular internalization. Whilst early studies have reported isolated cases of USPIO uptake in histologically benign, extra-axial tumors such as meningioma there also remains a paucity of studies in non-astrocytic, extra-axial tumors such as VS that sit outside the blood–brain barrier [29].

#### Cellular source of USPIO internalization in vivo

1.1.3.

The timing and mechanisms of USPIO trafficking into the brain and the exact cell-type specificity are yet to be fully understood. Previous *in vivo* models have demonstrated ferumoxytol localization within the lysosome of tumor CD68^+^/CD163^+^tumor macrophages, and within dilated astroglial end feet and astroglial processes in the parenchyma [30]. Data from human studies is limited to HGGs, and have shown iron deposition within CD68^+^/CD163^+^ TAMs following ferumoxytol (5 mg/kg) infusion, with significant positive correlations between delayed imaging and the number of CD68^+^/CD163^+^ iron-containing TAMs at time of tumor resection [26]. More recently, a study of 10 patients with IDH-wildtype GBMs, demonstrated that tissue samples from ferumoxytol enhancing regions contained significantly more M2 polarized macrophages than non-ferumoxytol enhancing tissue regions [28]. However, these studies are limited to high-grade tumors only, do not fully define the temporal relationship between vascular extravasation and intracellular uptake, nor assess their relative contributions to the evolving MRI signal. There is, therefore, a clear need for larger patient studies of USPIO-enhanced imaging in CNS tumors with comparative tissue datasets, to clarify the cellular source of the USPIO-enhanced MRI signal and evaluate the *in vivo* relationship between BBB disruption and USPIO extravasation.

### Objectives

1.2.

In this pilot study, we investigate the candidate USPIO agent ferumoxytol as a noninvasive imaging marker of TAM-driven inflammation in suspected transforming LGGs and VS. We hypothesize that delayed ferumoxytol-sensitive MRI signals reflect the transition from vascular circulation to extravascular and TAM-associated USPIO uptake within the tumor microenvironment.

The primary endpoint is to assess the association between delayed ferumoxytol-induced MRI susceptibility changes and histologically quantified TAM density, across CNS tumor subtypes with differing vascular and microenvironmental characteristics. Within this, the specific secondary endpoints are to:
Characterize the volume, pattern, and intensity of early and delayed USPIO-enhanced MRI signal in gliomas and VS and define the optimal qualitative (e.g., susceptibility-weighted imaging, SWI) and quantitative methods (e.g., quantitative susceptibility mapping, QSM and T2* mapping) for assessing delayed USPIO cellular internalization.Examine the relationship between GBCA enhancement patterns and the extent, spatial distribution and signal intensity of early (<2 hours) and delayed (24–48 hours) USPIO uptake in both glioma and VS cohorts.Examine the association between delayed USPIO-enhanced MRI signal, tissue markers of TAM abundance and VS clinical behavior, such as size and VS growth status.Evaluate QSM-derived susceptibility values as a quantitative imaging marker for detecting USPIO cellular internalization in CNS tumors, and the relationship with tissue measures of iron abundance and localization.Assess differences in USPIO-related signal changes and immune cell density between histologically confirmed transformed and non-transformed glioma regionsEvaluate the phenotype and spatial distribution of TAMs in each tumor and their relationship to USPIO uptake

Our specific hypotheses include that: (1) early (<2 hours) USPIO-enhanced imaging will principally reflect vascular distribution and will correspond with other MRI-derived measures of tumor vascular density and perfusion; (2) delayed (24–48 hours) USPIO-enhanced imaging will principally reflect intracellular USPIO distribution within TAM, and will co-localize with but also extend beyond imaging (GBCA enhancement) and tissue markers of endothelial disruption; (3) that QSM-derived susceptibility estimates and T2*-based measures will provide optimal quantitative reliable measures of TAM density, iron abundance and cellular iron localization with imaged tumors; (4) susceptibility based measures of delayed USPIO uptake (e.g., QSM, R2* mapping) will be greater in growing VS, relative to non-growing tumors, and will reflect an increased abundance of TAM in these tumors; and (5) that regions of higher grade transformation within imaged glioma will show changes on delayed USPIO-enhanced acquisitions, in particular susceptibility-based measures such as QSM, and these regions will show greater TAM abundance on matched tissue sections compared to non-enhancing tumor regions.

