During the study, a QSM protocol for visualizing absolute local magnetic field susceptibility changes resulting from cellular USPIO compartmentalization, will be optimized and evaluated. QSM differs from traditional hypo-intensity contrast in SWI or T_2_*, reflecting local rather than regional tissue susceptibility, overcoming blooming artifacts that arise through incorporating a dipole deconvolution during processing [35,36]. QSM data will be analyzed using the Morphology Enabled Dipole Inversion (MEDI) toolbox (v.2020), a widely validated pipeline for processing complex gradient echo data [36,37]. Early timepoint QSM maps are expected to reflect susceptibility shifts predominantly related to intravascular USPIO, whereas delayed maps (24 and 48 hours post-injection) are hypothesized to capture both residual intravascular USPIO and susceptibility effects, attributable to extravascular uptake by TAMs. Susceptibility values and spatial distribution patterns will be quantified across timepoints and evaluated alongside other multimodal maps, including DCE-MRI parameters and tissue data, to further explore the relationship between susceptibility changes, TAM infiltration and microenvironment features such as permeability and perfusion.

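### QSM is named as a marker of cellular USPIO uptake, but delayed QSM mixes compartments, and an unadjusted QSM–tissue correlation cannot separate how much iron there is from where it sits

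*Protocol article*

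**What the plan says.** Section 1.2 (Objectives) lists as its fourth secondary endpoint the evaluation of "QSM-derived susceptibility values as a quantitative imaging marker for detecting USPIO cellular internalization". The same item goes on to set tissue iron, both its amount and its location, as the comparator. Hypothesis 3 in the same section states that "QSM-derived susceptibility estimates and T2*-based measures will provide optimal quantitative reliable measures of TAM density, iron abundance and cellular iron localization". Hypothesis 2 adds that delayed "USPIO-enhanced imaging will principally reflect intracellular USPIO distribution within TAM".

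Section 2.5.1 (Post-scan processing) describes the delayed QSM maps differently: they "are hypothesized to capture both residual intravascular USPIO and susceptibility effects, attributable to extravascular uptake by TAMs". For SELFI, the same section lists USPIO remaining in the vessels among the possible distortions and says that SELFI must not be read by itself as evidence of uptake into cells. No matching caution is written for QSM.

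Section 1.1.2 gives the circulating half-life ("ferumoxytol, t½ = 14–21 hours") and says that USPIO leaks into the extravascular-extracellular space over roughly 24–48 hours. Section 2.3.1 places the delayed scans at 24 and 48 hours.

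Section 2.6 plans iron staining, Dx1 labelling, double-label immunohistochemistry and immunofluorescence, and LA-ICP-MS. Section 2.9 gives Pearson or Spearman correlation as the imaging–tissue method. It ties that method to the primary endpoint and names no separate method for the QSM–tissue endpoint.

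**The concern.** The endpoint and hypothesis 3 ask for information about where the iron is. Section 2.5.1 describes a value to which more than one compartment contributes, and no section explains how a single susceptibility value would tell them apart. Tissue that receives more USPIO will tend to have more of it both inside and outside macrophages. A QSM–tissue correlation can then be positive simply because some samples contain more iron than others.

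This matters because the distinction is what the study is for. Section 1.1.3 faults earlier work for not separating vascular leak from intracellular uptake in the MRI signal, and section 4 presents the study as able to ask whether TAM involvement is independent of barrier breakdown or vascular effects. If the QSM endpoint rests on an unadjusted correlation, it leaves the same gap, with wording that says it has been closed.

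**Working it through.** The plan states no figure on this point that could be reproduced. Two supporting calculations and one side-by-side reading apply.

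**1. Iron still circulating at the delayed scans.** Inputs: half-life h = 14 to 21 hours (section 1.1.2); scan times t = 24 and 48 hours (section 2.3.1). Assuming mono-exponential decay, the remaining fraction is 2^(−t/h).

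| Scan | h = 14 h | h = 21 h |
|---|---|---|
| 24 h | 2^(−24/14) = 0.305 | 2^(−24/21) = 0.453 |
| 48 h | 2^(−48/14) = 0.093 | 2^(−48/21) = 0.205 |

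These are fractions of the circulating agent, not of the tumor signal. The vascular part of a voxel also depends on its blood volume, which the documents do not give. The figures show only that the vascular contribution cannot be assumed away, least of all at 24 hours.

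**2. Compartments named for the same scans.** Section 2.5.1 names vessels and TAMs. Section 1.1.2 adds the extravascular-extracellular space. Section 1.1.3 reports, from earlier in vivo models, ferumoxytol in astroglial end feet and processes as well as in macrophages. So the protocol itself names more places for delayed iron than the one in the endpoint.

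**3. What an unadjusted correlation can show.** Illustrative model (an assumption, not a figure from the documents): QSM = I + N, where I is intracellular iron and N all other iron, independent of each other and measured without error. Let f = Var(I) / [Var(I) + Var(N)]. Then

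- corr(QSM, total iron) = 1
- corr(QSM, I) = Var(I) / √(Var(I) × [Var(I) + Var(N)]) = √f

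| f | 0.1 | 0.3 | 0.5 | 0.7 | 0.9 |
|---|---|---|---|---|---|
| corr(QSM, I) | 0.32 | 0.55 | 0.71 | 0.84 | 0.95 |

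By construction QSM holds no information on location here, yet it correlates positively with intracellular iron throughout. If I and N have equal variance and correlation ρ, the result is √[(1 + ρ)/2], which exceeds 0.71 for any positive ρ. Once total iron is held fixed, QSM has no variation left to relate to location. That is why adjustment for total iron is what separates the two readings.

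**4. Precision of an adjusted analysis.** The smallest correlation detectable with 80% power at two-sided 5% is tanh[(1.96 + 0.84)/√(n − 3)], which gives 0.67 for n = 15 (glioma) and 0.44 for n = 39 (all participants). With two adjusting variables the divisor becomes √(n − 5): tanh(2.80/√10) = 0.71 and tanh(2.80/√34) = 0.45. This assumes one sample per participant. The n = 39 figure is a best case, since section 2.2 includes participants considered for surveillance or drug treatment, who may give no tissue.

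**The case against.** The strongest reply is that the protocol does not rest internalization on a correlation of QSM with bulk iron. The endpoint goes on to name tissue localization as a comparator, hypothesis 3 covers QSM together with T2*-based measures, and section 2.6 provides cell-level localization. Section 2.5.1 states the mixed signal openly and reads QSM across timepoints and beside DCE-MRI and tissue data. Section 2.8 relates QSM to Ktrans, Ve and Vp and compares early with delayed imaging. The endpoint is secondary, in a feasibility-sized pilot, and evaluates a candidate marker, so a negative answer is allowed. Adjustment models are commonly left to an analysis plan that is not shown.

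Most of this stands. The absence of a written adjusted model is not a fault of the article, and the early-versus-delayed comparison does help with the vascular part. Two things remain. A cell-level reference does not separate amount from location if QSM is correlated with it unadjusted (step 3 of the working). And the wording of the endpoint and hypothesis is fixed in this document, where it goes further than section 2.5.1.

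A reader might infer more: that QSM is wholly insensitive to internalization, or that the study will report iron content as cellular uptake. The documents support neither. The first is a statement of general MR physics that they do not contain, and the second predicts how results will be written up.

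**Conclusion.** The point holds in a limited form. The fourth secondary endpoint and hypothesis 3 claim more for QSM than section 2.5.1 says the delayed maps contain, and section 1.1.2 adds a further compartment at the same times. A positive unadjusted correlation of QSM with tissue iron, or even with intracellular iron, would not by itself show internalization.

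The size rests on two assumptions. Mono-exponential decay leaves 30.5–45.3% of the agent circulating at 24 hours and 9.3–20.5% at 48 hours. The additive model gives correlations of 0.32–0.95 with intracellular iron, depending on its share of variance, with no location information in QSM. The argument that amount and location are confounded needs only that the compartments contribute jointly, which the protocol says. The consequence is a matter of wording and interpretation for one secondary endpoint. It does not invalidate the design.

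**What to change.** 1. In section 1.2, word the QSM-only claim as delayed USPIO iron abundance, and in hypothesis 3 separate abundance from cellular localization.
2. In section 2.5.1, give QSM the caution that SELFI already has: not to be read alone as evidence of uptake into cells.
3. State the condition for claiming internalization: the delayed change in QSM is associated, at ROI or sample level, with the tissue intracellular share (iron or Dx1 signal within Iba1-positive cells) after adjustment for total tissue iron and a vascular measure such as Vp. Treat several samples from one tumor as clustered. If QSM carries only iron amount, this test should be null, and the claim then stays at abundance.
4. As a separate exploratory analysis, relate the delayed change in R2* and R2, relative to the delayed change in susceptibility, to the same tissue share. This is not equivalent to item 3, because it can be positive when item 3 is null. Keep it at ROI level, since ratio maps are noisy.

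The cost is a few sentences and one derived measure, with no new scan or stain. The adjusted and ratio estimates will be imprecise at this sample size (working, step 4). They should also be read with the scan-to-surgery interval in mind. Section 2.4 expects up to 4 weeks in VS, and the Figure 1 caption has the particle coatings cleared at times beyond 14 days, so tissue localization, Dx1 in particular, may not represent the compartments imaged at 24–48 hours.

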### Data collection, management, and analysis

2.8.

Multimodal imaging analysis will assess the relationships between USPIO uptake and tumor vascular, microstructural, and inflammatory characteristics. Spatial associations will be examined between ferumoxytol-sensitive imaging markers (T_2_, T_2_*, SWI and SELFI values, QSM derived susceptibility values), ASL and DCE-MRI–derived microvascular parameters (*K*^*trans*^, *Ve, Vp*, blood flow), and diffusion metrics (mean diffusivity and fractional anisotropy) using voxel-wise and region-of-interest–based analyses. Early and delayed post-ferumoxytol imaging will be compared to assess time-dependent USPIO redistribution across vascular and extravascular compartments. In patients undergoing surgical resection, imaging-derived measures of USPIO uptake will be correlated with tissue-based markers of inflammation and microvascular proliferation. Spatially resolved elemental iron maps derived from LA-ICP-MS will be compared with adjacent histological sections to support spatial validation of imaging-defined USPIO uptake and compared with corresponding MRI-derived USPIO-sensitive metrics.

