### Statistical analysis

2.9.

Differences between ROI volumes on post-GBCA T_1_-weighted and delayed (24–48 hour) USPIO-enhanced T_1_-weighted images will be evaluated using overlap measures, the Dice similarity coefficient (DSC) and Jaccard similarity coefficients (JSC), and the Structural Similarity Index Measure (SSIM) [43,44].

To satisfy primary endpoints, the associations between imaging-derived and tissue-derived parameters will be assessed using Pearson’s product-moment correlation coefficient for approximately normally distributed variables, or Spearman’s rank correlation coefficient for non-parametric or non-linear associations. Secondary analyses will assess temporal changes in imaging metrics, spatial overlap between GBCA and delayed ferumoxytol signal, and associations between USPIO-sensitive metrics and DCE-MRI, ASL and DTI-derived parameters. Comparisons between tumor subgroups, including glioma subtype and VS growth status, will be performed using t-tests or ANOVA where assumptions are met, or suitable non-parametric alternatives where appropriate [14]. These subgroup analyses will be exploratory and interpreted as hypothesis-generating.

Temporal changes in voxel-wise and whole tumor ROI imaging metrics (T_2_, T_2_*, R_1_, QSM-derived susceptibility values) within each tumor voxel will be evaluated using a repeated-measures ANOVA with Greenhouse–Geisser correction for non-sphericity and repeated-measures mixed-effect modeling [45]. Mixed-effects modeling will be preferred where repeated-measures datasets are incomplete. To address multiplicity, analyses will be pre-specified by endpoint hierarchy. For ROI-based secondary analyses involving multiple imaging metrics, false discovery rate correction or Holm–Bonferroni correction will be applied as appropriate. Voxel-wise analyses will be treated as exploratory and will use spatially appropriate correction methods, such as cluster-level correction or false discovery rate correction, where feasible. Findings from these exploratory analyses will be interpreted as hypothesis-generating, rather than confirmatory.

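### Hypothesis 3 and the first secondary endpoint claim that some metrics are optimal, but no stated analysis compares how well the metrics track tissue

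*Protocol article*

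**What the plan says.** **The aim.** The Abstract says the pilot will "identify optimal imaging methods for this TAM quantification". In section 1.2 (Objectives), the first secondary endpoint is to "define the optimal qualitative (e.g., susceptibility-weighted imaging, SWI) and quantitative methods", the latter being "quantitative methods (e.g., quantitative susceptibility mapping, QSM and T2* mapping) for assessing delayed USPIO cellular internalization". Hypothesis 3 in the same section then names the expected winners: "QSM-derived susceptibility estimates and T2*-based measures will provide optimal quantitative reliable measures of TAM density". The sentence goes on to iron abundance and cellular iron localization.

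**The candidates.** Section 2.8 lists the ferumoxytol-sensitive markers as "T_2_, T_2_*, SWI and SELFI values, QSM derived susceptibility values", which makes five.

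**The analysis.** Section 2.8 says that in surgical patients "imaging-derived measures of USPIO uptake will be correlated with tissue-based markers of inflammation and microvascular proliferation". Section 2.9 says that, for the primary endpoints, "the associations between imaging-derived and tissue-derived parameters will be assessed using Pearson" or Spearman coefficients, depending on distribution and linearity. Its secondary analyses cover change over time, overlap of gadolinium and delayed ferumoxytol signal, associations with DCE-MRI, ASL and DTI parameters, and subgroup comparisons. FDR or Holm-Bonferroni correction applies to ROI-based secondary analyses with several imaging metrics.

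**The concern.** To call a metric optimal is to say that it does better than the alternatives. The matching statistical question is whether one metric's correlation with the tissue measure exceeds another's in the same patients. A correlation computed metric by metric answers a different question: whether that metric is associated with tissue at all. That can be true of every candidate at once.

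If the plan is followed as written, the only material for naming an optimum is a set of separate coefficients or p-values. A list of coefficients always has a largest member, and with few patients some will pass a significance threshold and others miss it by chance. Multiplicity correction limits false claims of association across the set. It does not turn those claims into a comparison.

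What is at stake is the choice of metric for the larger studies that this pilot is meant to inform.

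**Working it through.** **1. Match each comparative statement to an analysis.**
- Section 2.9, correlations: each metric against tissue, with no comparison between metrics.
- Section 2.9, Dice, Jaccard and SSIM: gadolinium against delayed ferumoxytol regions, with no tissue.
- Section 2.9, t-tests or ANOVA: tumor subgroups, not metrics.
- Section 2.9, repeated-measures models: change in each metric over time.
- Section 2.5.1, SELFI against relaxometry and QSM maps: image against image, with no tissue.
- Section 2.8, LA-ICP-MS iron maps against MRI metrics: image against tissue, but with no stated contrast between metrics.

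None tests or estimates a difference between metrics in how well they follow tissue, and no criterion for an optimum is given.

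**2. Inputs for an illustration.** The article gives no alpha, effect size or power, so there is no planned figure to reproduce. The planned total is 12 + 12 + 15 = 39. The number with tissue is not stated. I take n=15 (all gliomas) and n=27 (15 gliomas + 12 sporadic VS, all giving tissue, which is optimistic). Further assumptions are two-sided alpha 0.05, multivariate normal data, five metrics with the same true correlation ρ with TAM density, and correlations between metrics of 0.5 to 0.8.

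**3. Formulas.** Each metric is tested by t = r·√[(n−2)/(1−r²)] on n−2 degrees of freedom. The direct comparison is Williams' test for two correlations sharing the tissue variable:

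T = (r₁−r₂)·√{ (n−1)(1+r₁₂) / [ 2·((n−1)/(n−3))·D + r̄²·(1−r₁₂)³ ] }, on n−3 degrees of freedom,

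where r₁₂ is the correlation between the two metrics, r̄ = (r₁+r₂)/2 and D = 1 − r₁² − r₂² − r₁₂² + 2r₁r₂r₁₂.

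**4. Results when all five metrics are equally good** (20,000 simulated studies per setting; ranges cover the between-metric correlations):

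| True ρ | n | QSM or T2* significant, unadjusted | With Holm over five |
|---|---|---|---|
| 0.3 | 15 | 27-31% | 11-12% |
| 0.3 | 27 | 43-50% | 22-26% |
| 0.5 | 15 | 62-69% | 38-43% |
| 0.5 | 27 | 87-91% | 70-78% |
| 0.7 | 15 | 94-97% | 84-90% |

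QSM or T2* has the largest coefficient in about 40% of studies, which is simply 2/5. If SWI is left out because the endpoint lists it as qualitative, this becomes 2/4 = 50%. QSM or T2* is significant with no rival significant in 0-11%.

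**5. The direct comparison.** Under the same equality, Williams' test of QSM against one rival rejects in about 5%. For a real difference of 0.7 against 0.5, with between-metric correlation 0.6-0.8, its power is 18-31% at n=15, 32-57% at n=27 and 44-74% at n=39.

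**6. Precision of a single coefficient.** By Fisher's z, tanh(atanh(r) ± 1.96/√(n−3)), an observed r of 0.5 has a 95% interval of −0.02 to 0.81 at n=15 and 0.15 to 0.74 at n=27. Ranking point estimates with this much uncertainty says little.

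**The case against.** **The method may sit in an analysis plan that is not shown.** The choice among methods for dependent correlations is indeed a detail for such a plan. But the article does state an imaging-to-tissue analysis and a multiplicity rule across metrics, and neither addresses the comparison that its own hypothesis makes. That mismatch is visible in the document.

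**Correlation is the right tool for the primary endpoint.** This stands. The primary endpoint is an association, and nothing here criticizes it.

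**A reader might infer that each correlation will be tested against zero and that a significant result will count as confirming hypothesis 3.** The article does not say so. It names coefficients but no null value, alpha or success rule. The multiplicity corrections imply p-values, and zero is the usual null, but how the optimum will be judged is left open.

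**A reader might also infer that QSM or T2* is bound to look supported.** The figures do not bear that out. At a true correlation of 0.3 and n=15 the chance is 27-31%, and Holm lowers it further. When all metrics are equal, the rivals are often significant too, so QSM or T2* seldom stands out alone.

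**Optimal may mean more than the size of a correlation with TAM density.** This is fair. Hypothesis 3 also covers iron abundance and localization, the endpoint concerns cellular internalization, and SWI is listed there as qualitative. Whichever tissue measure is meant, the comparison between metrics is still absent.

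**This is a feasibility-sized pilot giving preliminary effect sizes.** This stands as an argument against a confirmatory gate. It is not an argument against estimating the effect that matters for choosing a metric, which is the difference between the correlations.

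**Conclusion.** The point holds as a mismatch between claim and analysis. Hypothesis 3 and the first secondary endpoint are comparative, while the stated analysis gives one correlation per metric and cannot separate superiority of QSM or T2* from equal performance of all metrics. FDR or Holm correction leaves this as it is.

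The size depends on assumptions that the article does not supply, chiefly the true correlation, the number of patients with tissue and the overlap between metrics. With equally good metrics, the chance that QSM or T2* reaches unadjusted significance runs from about 27% (ρ=0.3, n=15) to about 91% (ρ=0.5, n=27), and higher at ρ=0.7. The figures illustrate that a significant correlation is weak evidence for an optimum. They do not predict what the study will report. The primary endpoint is unaffected. This is a cheap improvement.

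**What to change.** In section 2.9, add for hypothesis 3 and the optimal-method endpoint: metrics will be compared by the difference between their correlations with the same tissue measure in the same patients, with a 95% confidence interval (Williams, Steiger or Meng method, or a patient-level paired bootstrap). The differences will be reported as exploratory estimates, and metrics will be described as not distinguished where the interval includes zero.

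Two details are needed. Name the tissue measure for each claim (TAM density or an iron measure). Orient all metrics the same way before taking differences, for example R2* rather than T2*, since a rise in iron moves T2* and susceptibility in opposite directions.

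Alternatively, reword hypothesis 3, the endpoint and the matching line of the Abstract so that they claim association only.

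The cost is a few lines of text and code on data already to be collected. The downside is that at these sample sizes the intervals will be wide, and the pilot will often be unable to name an optimum.
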